### Methods in analysis to handle protocol non-adherence and any statistical methods to handle missing data {20c}

In accordance with the principle of ITT analysis, we will analyze the results of the primary outcome by participant randomization, regardless of patients' adherence to the intervention. The worst-case imputation method will be used to handle missing data for primary efficacy data.

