#### Secondary outcomes

Secondary outcomes included the mean change from baseline to week 13 in the habitual-corrected visual acuity at distance in the AE, the contrast sensitivity in each eye, the stereoacuity at near and distance, the interocular suppression measured by worth-4 dot at near and distance, and the interocular suppression measured by Bagolini striated lens at near and distance, the treatment adherence and safety reports. Additional outcomes included all the measures at week 2, 4, and 9 for the analysis of within-person changes over time.

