### Sample size {14}

According to the requirements of the Good Clinical Practice for Medical Devices ([2022] No. 28) and the Guidance for the Design of Medical Device Clinical Trials, sample size estimation will be performed referring to the clinical study results of comparable medical devices of the investigational medical device and clinical expert opinions.

In this study, the sample size will be calculated based on the primary endpoint, namely the total effective proportion at 13 weeks, using the superiority design. Considering the treatment effects are strongly age-dependent, the participants are divided into 2 groups based on ages: Subgroup I (aged 5 to under 18 years) and Subgroup II (aged 18 to under 55 years).

Subgroup I: Based on clinical expert opinions and preliminary study results (unpublished data), the anticipated effective proportion at 13 weeks of the intervention group will be 75%, while that of the control group, based on previous literatures [10, 21, 22] and clinical expert opinions, will be 40%. With a superiority margin of 0 and a 1:1 ratio of intervention group to control group, the sample size required for each group is 28, as calculated using the PASS 2022 software, at the 5% significance level (two-sided) with 80% power. Considering the 15% dropout proportion during the study, 33 patients will be included in the intervention group and the control group, respectively, in patients aged 5 to under 18 years.

Subgroup II: Based on expert opinions and preliminary study results (unpublished data), the anticipated effective proportion at 13 weeks of the intervention group will be 60%, while that of the control group, based on previous literature [23, 24] and clinical expert opinions, will be 20%. With a superiority margin of 0 and 1:1 ratio of intervention group to control group, the sample size required for each group is 20 as calculated using the PASS 2022 software, at the 5% significance level (two-sided) with 80% power. Considering the 15% dropout proportion during the study, 24 patients will be included in the intervention group and the control group, respectively, in patients aged 18 to under 55 years.

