## Statistical methods

### Statistical methods for primary and secondary outcomes {20a}

The normal quantitative variables will be described as the mean and standard deviation (SD), and other quantitative variables will be described using the median and interquartile range. Categorical variables are described as the number of cases and the percentage of each category. Independent-sample T test or Wilcoxon rank-sum test will be used for the comparison between groups of quantitative variables based on the data distribution characteristics, and chi-square test or exact probability test will be used for categorical variables.

Statistical analysis will be performed using the SAS 9.4 (or above). Unless specified, all statistical tests will be two-sided at the 5% significance level, and the difference is considered statistically significant when the p value is ≤ 0.05. The analysis will be performed on an intention-to-treat and also per-protocol approaches. No interim analyses are planned.

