#### Analysis of secondary endpoints

The secondary efficacy endpoints are analyzed based on the FAS and PPS. The statistical methods for secondary efficacy endpoints follow the general principles of statistical analysis described above.

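### For the continuous secondary visual-function endpoints, the named two-sample test on change to week 13 uses only patients seen at week 13; a repeated-measures model on visits already collected would be a modest improvement

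*Protocol article*

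**What the plan says.** All references are to the protocol article.

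- **Endpoint.** Secondary outcomes: "Secondary outcomes included the mean change from baseline to week 13 in the habitual-corrected visual acuity at distance in the AE", followed by contrast sensitivity, stereoacuity, two suppression tests, adherence and safety. The same section makes the measures at weeks 2, 4 and 9 additional outcomes, for within-person change over time.
- **Analysis set.** Analysis of secondary endpoints: "The secondary efficacy endpoints are analyzed based on the FAS and PPS". Analysis datasets defines the FAS as consented, randomised participants under the intention-to-treat principle.
- **Method.** Analysis of secondary endpoints: "The statistical methods for secondary efficacy endpoints follow the general principles of statistical analysis described above". Those principles, in section {20a}, are: "Independent-sample T test or Wilcoxon rank-sum test will be used for the comparison between groups of quantitative variables", according to the distribution, and "chi-square test or exact probability test will be used for categorical variables".
- **Missing data.** Section {20c} has one rule: "The worst-case imputation method will be used to handle missing data for primary efficacy data". Its intention-to-treat sentence has the same scope: "we will analyze the results of the primary outcome by participant randomization, regardless of patients' adherence to the intervention".
- **Dropout.** Sample size {14} inflates each age group with the words "Considering the 15% dropout proportion during the study".
- **Visits.** Table 1 schedules acuity, contrast sensitivity and stereoacuity at baseline and at weeks 2, 4, 9 and 13.

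**The concern.** A two-sample test on change from baseline to week 13 needs a week-13 value for each patient. Unless some value is supplied for those who leave early, they drop out of the comparison even though it is labelled FAS. Earlier visits cannot enter such a test directly, and as stated it adjusts neither for the baseline value nor for the age stratum used in randomisation.

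Reasons for leaving could plausibly differ between the arms. Patients are not masked. Section {11b} lists adverse events, unwillingness and loss to follow-up as routes out, and section {22} expects diplopia, headache, nausea and eye strain. If early response drives leaving in one arm and not in the other, the patients still present at week 13 are selected differently by arm, and the comparison is biased. What is at stake is the estimated effect on the continuous secondary endpoints. The superiority claim does not depend on it.

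**Working it through.** **1. The plan's own figures.** The formula in Sample size {14}, with two-sided 5% significance, 80% power and margin 0, is n = (1.960 + 0.842)² × [P_C(1 − P_C) + P_T(1 − P_T)] / (P_T − P_C)².
- Under 18 years (75% v 40%): 27.39, so 28 per arm; 28/0.85 gives 33.
- Adults (60% v 20%): 19.62, so 20 per arm; 20/0.85 gives 24.
- Total: 2 × (33 + 24) = 114.

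These reproduce the stated numbers.

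**2. Patients outside the week-13 test.** 0.15 × 114 = 17.1, so about 17 without a week-13 value and about 97 with one (57 × 0.85 ≈ 48 per arm). The 15% is a planning allowance, so this is an expected size and not a known count.

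**3. Precision.** The smallest difference detectable with 80% power, in SD units, is 2.802 × √(2/n).
- 48 per arm: 0.57.
- 57 per arm: 0.52.

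The gap is the most that any fix could recover if every patient contributed fully.

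**4. Bias from unequal dropout rates.** Suppose early leavers do g SD worse than completers in both arms, with dropout proportions d_T and d_C. Each completer mean exceeds the mean of all randomised patients by d × g, so the bias of the difference is (d_T − d_C) × g. For g from 0.5 to 1.0:
- 15% v 15%: 0.
- 10% v 20%: 0.05 to 0.10 SD in size.
- 5% v 25%: 0.10 to 0.20 SD in size.

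**5. Bias from different dropout mechanisms at equal rates.** Assume 57 per arm, SD 1, a correlation of 0.5 to 0.85 between successive visits, and 15% leaving after week 4: at random in one arm, mainly poor early responders in the other. Over 4,000 simulated trials per setting:
- Completer comparison: bias about 0.06 SD at correlation 0.5, rising to about 0.16 SD at 0.85; standard error about 0.2.
- Likelihood-type estimate using the earlier visits: bias about 0.
- Random dropout in both arms: both unbiased; the likelihood-type estimate is 0 to 3% more precise.

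A hand calculation gives the ceiling. If exactly the lowest 15% at week 4 left one arm, the remaining week-4 mean would rise by φ(−1.036)/0.85 = 0.233/0.85 = 0.274 SD. Week 13 is two visits later, so the shift carried forward is 0.274 × ρ²: 0.07 at ρ = 0.5 and 0.20 at ρ = 0.85. The simulated values lie below this, as they should when dropout only leans towards poor responders.

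The SD, the correlations, the timing of dropout and its split by arm are all assumptions; the document gives none of them.

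**The case against.** The strongest objection is that this is an article condensing a fuller protocol, with a statistical analysis plan not shown, and that a missing-data rule for secondary endpoints is commonly left there. A t or Wilcoxon test can also be run on imputed values, so naming the test does not by itself settle who is dropped. Both points stand, and the absence of an imputation rule is not treated here as an error. What remains is a stated choice of test. That test cannot use the earlier visits without a separate imputation step, and it leaves out baseline and the stratification factor.

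A reader might infer more than the documents support:
- *That early leavers have no score on any secondary endpoint.* Adherence and safety are secondary outcomes and can be scored for them. Suppression by Worth 4-dot and Bagolini, if categorical, falls under chi-square or exact tests.
- *That the week 2, 4 and 9 data are discarded.* The Objectives compare the groups at each follow-up visit, and Secondary outcomes uses these visits for change over time. They are absent only from the week-13 test.
- *That leavers certainly have no final measurement.* Section {18b} plans an assessment before therapy stops, if feasible. It does not say whether that assessment counts as week 13.
- *That the FAS and per-protocol results would coincide.* The per-protocol set also excludes major protocol violations.

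It is also fair that the bias depends on the chosen mechanism, and that the simulated dropout depends on observed response, which is the condition under which the likelihood method does well. Leaving because of device symptoms need not be explained by recorded acuity, so the missing-at-random assumption may not hold exactly.

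**Conclusion.** The point holds for the continuous secondary visual-function endpoints only: habitual-corrected acuity, contrast sensitivity and, on a suitable continuous scale, stereoacuity. As written, their week-13 comparison rests on patients observed at week 13, leaving out about 17 of 114 at the assumed dropout. The resulting bias could be about 0.06 to 0.16 SD, at most about 0.8 of a standard error (0.16/0.2), under response-dependent dropout in one arm. It is about 0 if dropout is random or acts alike in both arms, and the precision gain is then small. The primary endpoint has its own rule, superiority is judged on that endpoint alone, and the sample size does not change. This is a minor improvement to a stated analysis choice.

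**What to change.** In Analysis of secondary endpoints, make the main FAS analysis of the continuous visual-function endpoints a mixed model for repeated measures on weeks 2, 4, 9 and 13. Include treatment, visit, treatment-by-visit interaction, baseline value and randomised age stratum, and report the week-13 treatment contrast. Keep the t or Wilcoxon test as a sensitivity analysis, and retain the Wilcoxon test for clearly non-normal scores. Adherence, safety and categorical suppression outcomes stay as planned.

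The cost is a change of wording and modest programming, with no new visits, data or patients. The downside is reliance on a missing-at-random assumption, which is weaker than what the completer comparison needs.

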### Outcomes {12}

#### Primary outcomes

The total effective proportion of amblyopia treatment at week 13. The effective amblyopia treatment is defined as at least 0.2 logMAR improvement of the BCVA at distance in the AE from baseline after treatment, measured with cycloplegic refraction using electronic ETDRS chart. The effective proportion will be calculated for each group.

Effective proportion (%) = Total number of patients meeting the criteria for effective amblyopia treatment/Total number of patients receiving amblyopia treatment in the analysis set × 100.

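### The 15% dropout inflation assumes dropouts leave the analysis, but the plan keeps them with worst-case imputation, so per-subgroup full-analysis-set power at 15% missing is about 73% rather than 80%

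*Protocol article*

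**What the plan says.** Under Sample size {14}, each age subgroup is powered separately "at the 5% significance level (two-sided) with 80% power", with superiority margin 0 and 1:1 allocation.

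- **Subgroup I** (5 to under 18 years): "the anticipated effective proportion at 13 weeks of the intervention group will be 75" per cent, with the control rate, "based on previous literatures [10, 21, 22] and clinical expert opinions, will be 40" per cent. This gives 28 per arm, and then "Considering the 15% dropout proportion during the study, 33 patients will be included in the intervention group and the control group".
- **Subgroup II** (18 to under 55 years): "the anticipated effective proportion at 13 weeks of the intervention group will be 60" per cent, with the control rate, "based on previous literature [23, 24] and clinical expert opinions, will be 20" per cent. This gives 20 per arm, raised to 24 for the same 15% dropout.

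Under Analysis datasets, the full analysis set (FAS) holds everyone who consented and was randomised, following intention to treat. The per-protocol set (PPS) holds those who completed the primary evaluation without major violations. Section {20c} says the primary outcome is analysed as randomised, whatever the adherence, and adds: "The worst-case imputation method will be used to handle missing data for primary efficacy data". It does not define the term. The denominator of the effective proportion is "Total number of patients receiving amblyopia treatment in the analysis set".

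Analysis of primary endpoint requires the lower Newcombe 95% limit for the difference to exceed 0 within the subgroups, and provides both FAS and PPS results.

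**The concern.** Dividing the evaluable number by 0.85 is the right adjustment when dropouts disappear from the denominator and the assumed rates hold among those who remain. Here they do not disappear. They stay in the FAS with an unfavourable imputed value. If that value is non-response, it lowers both success rates and shrinks their difference, and the sample size section makes no allowance for this. The stated 80% would then not describe the intention-to-treat analysis of the primary outcome.

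A second issue follows from the same rule. Patients are not masked, and the protocol itself expects poor adherence to patching. If more patients are lost from the patching arm, counting missing as not effective moves the comparison towards AR training, so the rule is not necessarily conservative.

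**Working it through.** **Inputs.** Sample size {14}: rates 0.75 vs 0.40 and 0.60 vs 0.20; two-sided 5%; 80% power; margin 0; 15% dropout. Analysis of primary endpoint: Newcombe 95% lower limit > 0.

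**1. Reproduce the plan.** The protocol's formula is n = (1.960 + 0.842)² × [P_C(1−P_C) + P_T(1−P_T)] / (P_T − P_C)², with (1.960 + 0.842)² = 7.849.

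- Subgroup I: 7.849 × (0.24 + 0.1875) / 0.35² = 27.39, so 28. Then 28/0.85 = 32.9, so 33.
- Subgroup II: 7.849 × (0.16 + 0.24) / 0.40² = 19.62, so 20. Then 20/0.85 = 23.5, so 24.

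All four figures match the protocol.

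**2. Rates in the FAS if 15% are missing in each arm and counted as not effective.** This takes 75/40% and 60/20% as completer rates, as the inflation implies.

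- Subgroup I: 0.75 × 0.85 = 0.6375; 0.40 × 0.85 = 0.34. The difference falls from 35 to 29.75 points.
- Subgroup II: 0.60 × 0.85 = 0.51; 0.20 × 0.85 = 0.17. The difference falls from 40 to 34 points.

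**3. Power by the protocol's formula**, Φ(difference / SE − 1.960).

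- Subgroup I, n = 33: SE = √[(0.6375×0.3625 + 0.34×0.66)/33] = √(0.4555/33) = 0.1175. 0.2975/0.1175 − 1.960 = 0.572, so power is 71.6%.
- Subgroup II, n = 24: SE = √[(0.51×0.49 + 0.17×0.83)/24] = √(0.391/24) = 0.1276. 0.34/0.1276 − 1.960 = 0.704, so power is 75.9%.

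**4. Power under the Newcombe rule**, by summing binomial probabilities over every outcome pair whose lower limit exceeds 0.

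| Scenario | Subgroup I: formula / Newcombe | Subgroup II: formula / Newcombe |
|---|---|---|
| Planned evaluable n (28, 20), none missing | 80.9% / 76.3% | 80.7% / 75.3% |
| 33, 24; 5% missing = not effective | 82.1% / 82.0% | 83.8% / 80.9% |
| 33, 24; 10% missing | 77.0% / 77.6% | 80.0% / 77.0% |
| 33, 24; 15% missing | 71.6% / 72.8% | 75.9% / 72.9% |
| 33, 24; 20% missing | 66.2% / 67.6% | 71.6% / 68.8% |

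Measured like for like against the first row, 15% missing costs 76.3 − 72.8 = 3.5 and 75.3 − 72.9 = 2.4 points under Newcombe, or 80.9 − 71.6 = 9.3 and 80.7 − 75.9 = 4.8 points on the sizing formula's scale.

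**5. Unequal missingness with no true effect.** The splits are illustrative assumptions; the protocol gives only 15% dropout overall. Take 10% missing under AR and 25% under patching.

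- Subgroup I, true 40% in both arms: 0.40 × 0.90 = 36% vs 0.40 × 0.75 = 30%, or +6 points. The chance that the lower limit exceeds 0 is 7.9%, against 2.7% with 15% missing in each arm.
- Subgroup II, true 20% in both arms: 18% vs 15%, or +3 points. The chance is 4.5%, against 2.4% with 15% missing in each arm.

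**The case against.** Five points can be made for the plan.

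- **The rates may not be completer rates.** If 75/40% and 60/20% already count dropouts as failures, Newcombe power at 33 and 24 is 86% and 84%. The protocol does not say so, and no inflation would then have been needed. The possibility stands but is the less natural reading.
- **Dropout need not mean missing data.** Section {18b} plans a final assessment before therapy stops, where feasible. This stands: lower missingness narrows the gap, and at 5% there is none.
- **The PPS is also reported**, and the inflation suits an analysis of completers. True, but {20c} applies intention to treat to the primary outcome.
- **Not all of the gap comes from imputation.** This stands. A reader might infer that dropout handling explains the whole fall from 80% to 73%. Under Newcombe, power is already 76.3% and 75.3% with complete data at the planned evaluable numbers, because the sizing formula and the decision rule differ.
- **Counting dropout as failure can be a legitimate definition of the endpoint.** On that definition the +6 points is a real difference, not bias. That is fair, and it is why unequal missingness calls for a sensitivity analysis rather than a different primary rule.

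Two stronger readings are tempting. One is that power is only about a quarter: if worst case meant failure for AR and success for patching, the rates would be 63.8% vs 49% and 51% vs 32%, with Newcombe power 25.6% and 28.5%. The protocol does not state that rule, and an analysis plan not shown may define the term, so these figures are conditional only. The other is that the trial's false-positive rate is inflated. The dropout splits are assumed. If superiority must hold in both subgroups and neither has a true effect, the joint rate in the example is about 0.079 × 0.045 = 0.4%.

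**Conclusion.** The mismatch is real and lies within the protocol: the sample size treats dropouts as removed, the primary analysis keeps them, and the assumed rates are not lowered to match. With 15% missing in each arm, missing counted as not effective, and the planning rates read as completer rates, per-subgroup FAS power is 71.6% and 75.9% on the protocol's formula, or about 73% in both under its decision rule. The size depends on the missingness actually seen.

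The undefined imputation term needs one clarifying sentence; the text does not support treating its most extreme meaning as the plan. This should be fixed, but it does not invalidate the design.

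**What to change.** 1. In {20c}, state that a missing week-13 best-corrected acuity counts as not effective in both arms, with all randomised patients as the denominator, and align the denominator wording under Primary outcomes.
2. In {14}, restate per-subgroup FAS power as about 73% at 15% missing, with the range: about 78% and 77% at 10%, and above 80% at 5%.
3. Prespecify two sensitivity analyses: multiple imputation of week-13 acuity from baseline and weeks 2, 4 and 9, which Table 1 already schedules; and the extreme case of failure for AR and success for patching, noting that its power at 15% missing is about 26% and 29%.

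Multiple imputation is better placed here than as the primary method. Making it primary is a debatable trade-off, and the restated 73% would not be the power of that analysis.

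The cost is a lower stated power, some wording and a little more analysis. No new data are needed. The Trial status section reports 43 of 114 enrolled and no interim analysis is planned, so if analysis has not begun the change can be made before results are seen.

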### Plans to give access to the full protocol, participant-level data, and statistical code {31c}

The full protocol, de-identified datasets, and statistical code may be made available from the corresponding author upon reasonable request and appropriate resources after the final publication of results.

## Oversight and monitoring

### Composition of the coordinating center and trial steering committee {5d}

Daily support for the trial is provided by:Principal investigators: supervise the trial and are responsible for the medical responsibility of the patients, identify potential recruits, and take informed consent;Sub-investigators: are responsible for the medical responsibility of the patients, identify potential recruits, register the trial registration;Contract Research Organization (CRO): develop the monitoring plan and monitor the conduct of the trial, assign qualified CRA to conduct regular on-site monitoring visits to the participant centers, so as to ensure that all the contents of the study protocol are strictly observed, and check the source data to ensure consistency with the contents on the electronic CRF;CRA: supervise the adherence of the investigators with the protocol, the GCP and relevant laws and regulations in the conduct of clinical trial, the signing of informed consent, screening, rights and interests and safety guarantee of the subjects, the management and use of the investigational medical device, the management of adverse events and device deficiencies, the reporting of safety information, and the recording of clinical trial data and completion of eCRF;DM: design case report forms (CRFs) aligned with the study protocol and implement an EDC system for centralized data management. A DVP will be developed by the DM pre-database activation, specifying system-generated automated queries and manual verification scopes.CRC: assist the PIs in performing daily management tasks of clinical trials, including the recruitment, informed consent, data collection, eCRF completion, and document management, organize data capture, ensure that trial operations comply with GCP and protocol requirements, coordinate participant follow-up visits, and communicate with CRA;Physicians: conduct follow-up examinations.

The study team meets biweekly. There is no trial steering committee or stakeholder and public involvement group.

